**Management of RTIs**

Prior to study enrollment, pelvic examination, Pap smear, and RTI screening will be conducted, and RTIs will be treated according to the latest Thai (1997) and CDC (1998) guidelines.

Participants will receive treatment for all curable RTIs free of charge. Treatment of genital ulcer disease will be syndromic and will include treatment for chancroid and syphilis, unless the ulcer disease is highly suspicious for herpes. Treatment of cervical and vaginal infection will be guided by RTI test results. At all visits where speculum examination is performed, vaginal pool specimen pH, and gram stain for BV and yeast will be conducted on samples collected from the posterior fornix. For women with symptoms or abnormal signs, stat gram stain, trich in-pouch, and KOH whiff test will be conducted, and results of the pH, KOH whiff, and gram stain will be available immediately following the examination. Women with symptomatic bacterial vaginosis (BV) or symptomatic candidiasis will therefore be treated at the same study visit. Results for the trichomonas culture results will be available within several days and for *C. trachomatis* and *N. gonorrhoeae* will be available within two weeks of the study visit, and women with positive results will be treated either at the next regularly scheduled follow-up visit or, if the study staff feel that it is warranted, the woman would be contacted (with her permission and in a manner that preserves confidentiality) to come to the clinic for an unscheduled visit. Study staff may treat severe cervicitis or symptoms of pelvic inflammatory disease syndromically at the study visit, it they feel that this is necessary to prevent sequelae.

During the study, genital ulcer disease will be treated syndromically including adequate therapy for curable etiologies (syphilis and chancroid). Amplicor genital ulcer PCR is not approved by the US or Thai FDA and is not routinely available in Thailand. Because PCR genital ulcer disease (GUD) specimen testing will be conducted after the study is completed, participants will be asked if they would like to be contacted and informed of their genital ulcer PCR test results (if this type of testing is conducted during the study). All women will have a pap smear as part of the study screening process and will be advised at enrollment to have regular annual pap smears. HPV testing will be conducted after the study is completed; Clinical management is not affected by these results, and results will not be provided to patients. Women with curable STIs (gonorrhea, chlamydia, trichomoniasis, or syphilis) will be given a card (with a code to indicate the infection type) to give to her partner(s), if she chooses, so that he/they can come to the clinic for testing and treatment. Participants’ partners will be treated for STIs free of charge.

Women with any curable RTI must be effectively treated prior to enrollment. Women may be enrolled after treatment, and women with treated chlamydia infection or gonorrhea may be enrolled after having a test of cure approximately four weeks after completing therapy and less than four weeks before enrollment. Women with syphilis may be enrolled once they are free of signs and symptoms of syphilis and if their RPR titer has declined at least four-fold following treatment. Women with treated trichomoniasis may be enrolled if there is no evidence of trichomoniasis on repeat trichomonas InPouch wet-mount & culture examination. Women with other persistent abnormal signs, such as vaginal or cervical discharge, despite treatment of identified RTI, may be enrolled. Women with symptoms of vaginal infection may be enrolled only if their current stat laboratory evaluation is negative for BV, candidiasis, and trichomoniasis. Women with asymptomatic BV or candidiasis may be enrolled. Women with laboratory evidence of or recent treatment for BV or candidiasis may be enrolled once asymptomatic. Women with persistent genital epithelial disruption on naked eye examination or colposcopy will not be enrolled.

All women will also be asked to give contact information so that they can be located in the event that they do not return to the clinic for a scheduled study visit. The study staff will explain to the women that attendance at scheduled follow-up visits is important, especially in the event that one of her laboratory tests shows a positive diagnosis of an STI for which she could be treated. The contact information, however, will not become part of the case record forms and will be kept in a locked filing cabinet, separate from the forms

## Partner HIV testing and informed consent

If the woman has a sex partner, he will be required to come to the clinic for an HIV test and to give his written, informed consent for her participation in the study prior to her enrollment because of his potential exposure to the study product. If she will not see or does not plan to be sexually active with her husband or steady sex partner during the study period, he does not need to come to the clinic for HIV testing and informed consent. Women will receive extensive counseling prior to study enrollment regarding the risk of HIV transmission from her to any sex partner. During the counseling sessions, she will be strongly encouraged to use condoms, and condom use will be reviewed. During the study screening and pre-enrollment process, women will be counseled regarding the importance of remaining abstinent or using condoms if she is sexually active during the study. If she initially plans not to be sexually active with her steady partner/husband during the study and her situation changes, she will be asked to bring him to the clinic for informed consent and HIV testing.

If women who had thought they would not see their steady sex partner or husband during the study report that they have become sexually active or if there is evidence that they are sexually active, they will be asked to bring him to the clinic for informed consent and HIV testing. Women who are not able to be compliant with the study protocol, especially if others may be at risk as a result, may be discontinued from the study at any time based upon the investigators’ discretion.

## Enrollment visit

After the woman has completed two screening visits and had an HIV care evaluation at Chiang Rai Hospital, she will come to the clinic for her first study visit ideally, 3-5 days after the end of her menstrual cycle. (This visit may occur up to 10 days following the end of her menstrual cycle if her day 14 visit is not expected to coincide with the estimated start of her next menstrual cycle.) The enrollment visit is the baseline visit of the first study arm. During the enrollment visit, the following will take place (see Tables 2 and 3):

- Review of STI results and treatment confirmation
- Confirm partner’s informed consent
- Informed consent for enrollment
- Enrollment form
- Interviewer-administered enrollment interview
- Urine pregnancy test
- pH, Gram Stain,
- Collection of blood sample for plasma viral load testing, HSV 1 and 2 antibody testing
- Baseline pelvic and colposcopic examinations
- Baseline CVL and vaginal swab sample collection for HIV cervico-vaginal viral load
- Clinician study form
- Study arm sequence randomization
- Product administration (if a product arm)
- Second pelvic and colposcopic examinations (to assess acute effects of the product on the vaginal epithelium)
- Second CVL and vaginal swab sample collection for cervico-vaginal HIV viral load (to assess acute effects of the product on cervico-vaginal HIV viral load)

The details of the study will be discussed again before enrollment, and women will be asked to sign an informed consent for study enrollment. Consent from the woman’s husband/steady partner is required because of his potential exposure to the gel, and this consent must be obtained prior to the participant’s enrollment in the study. He will be able to come to the clinic anytime after the woman has had her first screening visit and her enrollment visit to be tested and give his informed consent. A research nurse will administer the enrollment interview that includes questions concerning the participant’s reproductive health and sexual practices.

A pelvic examination will be conducted in which samples for RTI testing and cervico-vaginal HIV viral load will be collected, and colposcopy will be conducted. A rapid semen detection test will be conducted on the CVL to determine if the CVL is contaminated with semen which could effect the HIV viral measurement in the CVL, resulting in an inaccurate measurement of the study participant’s cervico-vaginal HIV viral load. If the CVL is contaminated with semen, this CVL and corresponding swab will be discarded, and the enrollment visit will be rescheduled within 48 hours.

Patients in whom the rapid semen detection test is positive will receive extensive counseling regarding risk of HIV transmission to sex partners and strongly encouraged to use condoms or remain abstinent during the study. Regardless of reported partner status, all study participants will be counseled to use condoms consistently throughout the study.

After the baseline examination and clinical specimen collection, women will be randomized to a study arm sequence. If the first arm of her study sequence is a product arm, she will be given instructions on how to insert the product and, while in the examination room, will vaginally insert the first applicator of gel. She will wait either in the examination room or in the waiting room. After approximately 15 minutes, another pelvic examination will be conducted, cervico-vaginal HIV viral load samples including 2 vaginal swabs and 2 CVL (unless further study indicates that only one is necessary) will be collected, and colposcopy will be done. Neither the woman nor the research team will know which of the two products she is using.

If the first study arm to which the participant is randomized is the arm of the study in which noproduct is used, she will also wait at the clinic for 15 minutes and will have a repeat pelvic examination with cervico-vaginal HIV sample collection and colposcopy.

Women assigned to a product arm will be instructed to insert the gel vaginally once daily for the following 6 days. Women will be given 7 applicators (one extra) to take home.

## Randomization and dispensing of study products

This study is a cross-over design in which each woman will participate in each of the 3 study arms. Once enrolled in the study, women will be randomized to one of six study arm sequences. Before the study begins, a pseudo-random number generator, available as part of the SPSS software package, will be used to generate a randomization scheme, assigning women to one of the 6 sequences, beginning with Carraguard, placebo, or a no product arm.

Individual envelopes will be prepared for each woman in the study, each containing a unique study identification number. Upon enrollment in the study, each woman will receive the next sequentially numbered envelope. The envelope will contain a code indicating to the study staff her study arm sequence, or the order in which she will participate in each of the three arms: Carraguard, placebo or no product. The study staff will refer to this code when distributing the study products to the participants. Additional participants added to maintain the number of evaluable subjects will be added in groups of six, randomized to one of the six study sequences.

Study gels will be packaged in boxes of eight applicators, with different colored seals indicating Carraguard or placebo. Once randomized, a participant will be considered enrolled in the study and will be included in the intention-to-treat analyses; only women who are started on antiretroviral therapy will be excluded from the intention-to-treat analysis.

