
## Design

Randomized, controlled, double-blind, three arm, cross-over trial

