# Product interruption criteria

Application of the study product will be interrupted in the following circumstances:

- Pregnancy
- Genital or other major surgery
- Medical condition incompatible with the study protocol or visit schedule
- SAE related to the investigational product
- Consent withdrawn
- Missed follow-up visit. However, at the investigators’ discretion, a participant may resume study participation (after her next menstrual period if menstruating)
- Lack of compliance

If an emergency, such as anaphylactic shock occurs, arises and it is necessary to unblind the product used by a particular participant, four individuals will have access to the randomization scheme, and can be reached both at work and at home, 24 hours a day, at the following telephone numbers:

[name] (NY): work: [contact] home: [contact]

[name] (NY): work: [contact] home: [contact]

[name] (NY): work: [contact] home: [contact]

[name] (Bangkok): work: [name] home: [name] [contact]

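### Gel boxes are coded by seal colour per product, so an emergency code break for one woman can reveal the gel allocation of all the others

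*Protocol*

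**What the plan says.** The Design section calls the study a "Randomized, controlled, double-blind, three arm, cross-over trial". Under Enrollment visit the blinding promise is explicit: "Neither the woman nor the research team will know which of the two products she is using".

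The section on randomization and dispensing describes how gel reaches the women. Each woman gets the next numbered envelope: "The envelope will contain a code indicating to the study staff her study arm sequence". Then: "The study staff will refer to this code when distributing the study products to the participants". Each box holds eight applicators, and the boxes come "with different colored seals indicating Carraguard or placebo".

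The Product interruption criteria provide for emergencies. If "it is necessary to unblind the product used by a particular participant, four individuals will have access to the randomization scheme". The list that follows places three of the four in New York and one in Bangkok.

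The Data analysis section makes epithelial disruption (colposcopic and naked-eye), flora disturbance, self-reported symptoms and RTI acquisition the primary safety endpoints. It also plans a check of epithelial disruption after 25 women have completed their first gel arm, which can stop enrollment.

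**The concern.** The mark on the box is tied to the product. It is not tied to a woman, a period or a kit. Every box of Carraguard therefore carries a mark that no placebo box carries, and the staff who dispense can see it at each gel period.

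Under such a code, unblinding cannot be confined to one woman once the answer reaches someone who knows her seal colour. That person then holds the key for the whole trial. The emergency provision is worded for a single participant, and the packaging rule defeats it.

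What is at stake is the Carraguard-placebo comparison of endpoints that rest on judgement. Epithelial disruption is read by an examiner and is exposed directly. Symptoms and acceptability are collected by an interviewer, so staff knowledge can reach them only indirectly. Shedding, Gram-stain flora and PCR or culture results are less exposed. Carraguard against no product is affected little, because the no-product arm is open in any case.

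**Working it through.** The Protocol states no figure on this point, so there is none to reproduce. The check counts what one disclosure reveals.

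**Inputs.** 60 women (Sample size, in the Study summary). Three arms per woman, two with gel (Methods, Overview). Six sequences, each containing both gels (Study arm sequences). Seal colour indicates product (Randomization and dispensing of study products).

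**Step 1: gel periods.** 60 × 2 = 120.

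**Step 2: one colour per gel (the plain reading).** Two colours can map to two gels in 2 ways. Learning the gel in any one period leaves 1 way. This holds for each gel period of all six sequences. The disclosure therefore reveals all 120 gel periods:
- 2 belong to the woman who was unblinded. Her second gel follows by elimination under any labelling, because of the cross-over.
- 120 − 2 = 118 belong to the other 59 women. These are the result of the seal code.

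**Step 3: timing.** An assessment already recorded cannot be biased by later knowledge. If a share f of the other women's gel periods has been assessed when the break occurs, 118 × (1 − f) remain exposed. The Protocol gives no f. The range runs from 118 (f = 0) to 0 (f = 1). At an assumed f = 0.5 it is 59.

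**Step 4: several colours per gel (assumption).** Suppose each gel has k colours, assigned at random and independently for each woman. Another woman is revealed if one of her boxes carries a decoded colour, since her other gel then follows by elimination.
- One colour decoded: share = 1/k.
- Both of the unblinded woman's colours decoded: share = 1 − (1 − 1/k)².

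| k per gel | One colour decoded | Both colours decoded |
|---|---|---|
| 1 | 100% (59 women) | 100% (59 women) |
| 2 | 50% (29.5) | 75% (44.2) |
| 3 | 33% (19.7) | 56% (32.8) |
| 5 | 20% (11.8) | 36% (21.2) |

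More colours shrink the leak but do not close it.

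**Step 5: codes unique to woman and period.** A break reveals no other woman.

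**Step 6: safeguards.** The Protocol describes no separation of dispensers from examiners or interviewers, no hiding or removal of seals before dispensing, and no rule on who at the site may learn the result of a code break.

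**The case against.** Much of the case on the other side stands.

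- **Chain of events.** Harm requires a code break, disclosure to someone who knows that woman's seal colour, and later assessment of other women by that person or by someone told. All four holders of the scheme are off site, and the Protocol does not say that the result goes to examiners or interviewers. The probability of this chain cannot be stated from the document.
- **Staff overlap.** A reader might infer that the same few people dispense, examine and interview. The Study site section lists five research nurses, four research assistants and others but does not assign these tasks, so the overlap is possible and not established.
- **Guessing.** A reader might infer that a correct guess at the colours unblinds the trial. It does not. With two mappings an uninformed guess is right half the time, and nothing confirms it. The Composition of placebo section says the two gels cannot be told apart by look, feel, smell or taste. A guess gives an unconfirmed belief, though one that would be applied across the trial.
- **Visibility.** The colour is on the seal of the box. The document does not say that applicators are coloured or that the examiner sees the box.
- **Number of colours.** More than one colour per gel is not excluded.

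These points limit the likelihood and the size. They do not reconcile the packaging rule with unblinding limited to one participant.

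**Conclusion.** The point holds as a conflict within the Protocol that is cheap to remove. A seal colour that stands for the product turns a single-participant code break into a possible trial-wide one. The upper bound is 59 other women and 118 further gel periods, and it falls as assessments are completed before the break. This rests on one colour per gel, which is the natural reading but is not stated, and on the disclosure reaching staff who know the colour.

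Two stronger readings should be set aside. One is that all 120 gel periods would be biased: that count is of allocations revealed, and periods already assessed are safe. The other is that the envelopes and seals tell staff openly which gel they are handing out. The Protocol describes codes, and names four off-site people as having access to the scheme in an emergency.

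The consequence is confined mainly to examiner-judged epithelial disruption in the Carraguard-placebo contrast, including the early mucosal safety check if a break came before it.

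**What to change.** Replace the product-linked seal colours with kit codes specific to woman and period, taken from the randomization list. No visible mark should be shared by all boxes of one gel. Hold one individual code-break record per woman. Amend the randomization and dispensing section accordingly, so that it agrees with the blinding promise under Enrollment visit and the single-participant unblinding under Product interruption criteria.

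If colours have to stay, use several per gel, assigned at random across sequences, and state how many. This is weaker: five per gel would still reveal 20% to 36% of the other women under the assumptions above.

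The cost is seal and label printing, slightly more packing and dispensing work, and a longer kit list for those who hold the code. No extra women, visits or staff are needed.

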The following plot shows the power to detect a statistically significant difference between a pair of treatments for varying effect sizes with an overall sample size of 30 or 50, at a significance level of 0.025 (based on the Bonferroni adjustment for the two planned pairwise comparisons, for an overall Type I error rate of 0.05). A horizontal line indicates 80% power. The effect size is based on the difference between a pair of treatment means on the log scale. Thus the plot shows that with a sample size of 30 and a within standard deviation of 0.6, there is at least 80% power to detect a difference between a pair of treatment means (on the log scale) of 0.55 or higher. On the other hand, with a sample size of 50 and a standard deviation of 0.6, there is at least 80% power to detect a difference between a pair of treatment means (on the log scale) of 0.43 or higher. The estimates of power would be higher if no carryover effect truly exists. Sixty women will be enrolled to account for participants lost to follow-up and participants who may start antiretroviral therapy and so there is an equal number of women in each study sequence.

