## Eligibility criteria

Women will be eligible to participate in the study if they fulfill all of the following inclusion criteria:

- Age 18-50 years
- Plan to stay in the Chiang Rai area for at least four months
- HIV-infected, confirmed by Elisa and Western Blot tests
- Either has 1) no current sex partner and is planning to be abstinent for the study duration, *or* 2) has only one, HIV-infected sexual partner1 who is 18 years or older and is willing to give informed consent for confirmatory HIV testing and for the participant’s enrollment in the study. Women who have a steady partner/husband who she will not see during the study period or with whom she is not sexually active will not be required to bring their partner to the clinic for HIV testing and informed consent.
- Willing and able to give informed consent
- Willing and able to comply with the study protocol, including being tested for HIV and undergoing repeated pelvic and colposcopic examinations
- Willing to have male partner asked for informed consent because he will be exposed to study product
- Regular menstrual cycles (defined as occurring every 3-5 weeks, lasting 3-5 days) for the prior 3 months; if have amenorrhea or if using depo-provera, participant must have no reported history of vaginal bleeding for the previous 3 months
- CD4 count < 5002
- Not currently taking antiretroviral medications3
- Documented Class I or Class II (“atypical cells seen, usually caused by inflammation”) pap smear at screening for study participation
- In good health as determined by medical history, physical examination and results of any laboratory screening test, and the discretion of the clinical staff
- Able to achieve a score of 80% or better on true-false test of key study concepts. If women score less than 80% the first time they take the test, they may repeat the test at least one day later

1We are including this criterion to minimize any potential risk of HIV transmission from study participants to a sexual partner.

2We are including this criteria because women with CD4 counts greater than 500 are much less likely to have cervical-vaginal HIV shedding.

3We are including this criterion because women who are on antiretroviral therapy are much less likely to have cervical-vaginal HIV shedding. Women who begin antiretroviral therapy while enrolled in the trial will be allowed to continue to participate in the trial.

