Relatively few people with HIV/AIDS in Thailand have access to antiretroviral therapy (ART) through limited programs sponsored by the Ministry of Public Health. Currently the largest such program provides ART to approximately 2,500 people nationwide out of the estimated 600,000 people with HIV/AIDS in Thailand. Access to these programs is controlled by district-level committees. This situation is evolving with ART becoming more generally available. ART will not be offered to participants as a part of this study. Offering such therapy as a benefit of study participation could be an unduly coercive incentive to enrollment, forcing women who would not otherwise do so to use the study gel. In addition, provision of ART requires long-term commitment and rigorous attention to adherence, response to treatment, emergence of resistance, and monitoring for side effects, beyond the scope of this limited research protocol. During the study, staff will facilitate access to available ART programs for study participants in collaboration with the Chiang Rai Hospital Department of Medicine. If women are started on antiretroviral therapy during the initial HIV evaluation, they will not be eligible for the study. Participants will not be prevented or discouraged in any way from initiating antiretroviral therapy once they enroll, if it becomes available to them. If this occurs, participants will continue to follow the same procedures as those who are not on antiretroviral therapy; This procedure will be re-evaluated if the situation changes in Thailand, e.g., if access to antiretroviral therapy is expanded to make the medications available to most patients. Both the Community Advisory Group in Chiang Rai and the Thai Ethical Review Council support our plan.

The data collected from a woman who begins antiretroviral therapy will be analyzed and described separately from the other study participants because antiretroviral therapy will affect the amount of cervico-vaginal HIV shedding.

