The definition of noncompliance is less than 6 days of study gel use reported at the first follow-up (7 day ) visit. Women who do not meet this criterion will be asked to use gel for up to 3 more days, for a maximum of 6 days. For the analysis, women who use study gel 6 of 9 days or more will be included in the per protocol analysis and those who do not meet this criterion will be included in the intention to treat analysis.

We will have a statistician review the mucosal safety data after the first 25 women have completed the first gel use arm. We will look at the differences in epithelial disruption (includes abrasions, ulcers, and fissures) from baseline to the first follow-up visit (day 7) and compare these differences between the 3 study arms. We will stop enrollment in the study and form a DMC to review the data if there is a difference between groups that is significant at the p<0.001 level, a standard stopping rule for this type of trial (Reference: Geller, N and Pocock, S. Interim Analyses in Randomized Clinical trials: Ramifications and Guidelines for Practitioners. Biometrics 43 1987 213-223).

Study participants will be provided with information regarding how to contact the Chiang Rai Health Center for study results and their blinding code when results are available. Results of the final analysis will be presented to the Chiang Rai Advisory Committee, and at local and international scientific meetings. We also plan to publish the results in the international scientific literature.

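### The set called intention-to-treat leaves out whole women who start antiretroviral therapy (ART) after randomisation, for a reason that covers only their post-ART shedding samples

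*Protocol*

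**What the plan says.** Under Randomization and dispensing of study products, the protocol first gives the usual definition: "Once randomized, a participant will be considered enrolled in the study and will be included in the intention-to-treat analyses". The same sentence then adds the exception: "only women who are started on antiretroviral therapy will be excluded from the intention-to-treat analysis".

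The HIV evaluation section says what happens to the excluded data, "The data collected from a woman who begins antiretroviral therapy will be analyzed and described separately from the other study participants", and gives one ground for it: "because antiretroviral therapy will affect the amount of cervico-vaginal HIV shedding". That section also makes a woman ineligible if ART is started at the initial HIV evaluation, so the exception concerns starts after enrolment.

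These women are not withdrawn. A footnote to Eligibility criteria says "Women who begin antiretroviral therapy while enrolled in the trial will be allowed to continue to participate in the trial", and the HIV evaluation section keeps them on the same procedures as everyone else. The event is foreseen in Sample size: "Sixty women will be enrolled to account for participants lost to follow-up and participants who may start antiretroviral therapy".

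Under Data analysis, the Objective 1 primary endpoints are epithelial disruption, vaginal flora disturbance, reported symptoms and acquisition of reproductive tract infections. No analysis set is named for them.

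**The concern.** An intention-to-treat set is fixed at randomisation. This one depends on something that happens later: whether a woman's first period counts depends on whether she starts ART in, say, her third.

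The stated ground is also narrower than the rule. An effect of ART on shedding is a reason to treat shedding samples taken after the start differently. It is no reason to set aside periods completed before the start, or colposcopy, flora, symptom and infection data at any time.

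At stake is mainly the safety comparison. In a study of 60 women, the Background section names epithelial disruption as a primary and critical endpoint. Women who start ART stay in follow-up and are examined on the same schedule. If the set as defined governs Objective 1, their results are collected and then left out of the randomised comparison for a reason unrelated to safety.

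**Working it through.** **1. The rule against its reason**

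| Data from a woman who starts ART | Under the rule as worded | Covered by the stated reason? |
|---|---|---|
| Shedding samples after the start | Out of the main comparison | Yes |
| Shedding samples from periods completed before the start | Out of the main comparison | No |
| Objective 1 data before the start | Out, if this set governs Objective 1 | No |
| Objective 1 data after the start | Out, if this set governs Objective 1 | No; no safety reason is given |

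**2. Reproducing the plan's power figures**

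Inputs from Sample size: three-period Williams design with six sequences, first-order carry-over in the model, within-woman SD 0.6, significance level 0.025 per comparison (taken as two-sided, because the hypotheses are of difference).

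With woman, period, treatment and carry-over terms, the variance of a treatment difference in a balanced design is (5/12) × SD² / (N/6).

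- N = 30: variance factor 0.08333; SE = 0.6 × √0.08333 = 0.173. For a difference of 0.55, 0.55/0.173 = 3.18, less 2.24, gives power 82.5% (normal) or 80.5% (t).
- N = 50: exact variance factor 0.04975; SE = 0.134. For a difference of 0.43, 0.43/0.134 = 3.21, less 2.24, gives 83.4% (normal) or 82.3% (t).

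Both of the plan's claims of at least 80% hold at SD 0.6. The step from 50 to 60 women allows for a loss of (60 − 50)/60 = 16.7%.

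**3. What whole-woman exclusion costs for shedding**

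The documents give no ART-start rate, so a range of 0 to 15 starters among 60 is assumed. Further assumptions: SD 0.6, difference 0.43, level 0.025, t-based power, start equally likely before period 2 or before period 3, no other loss, average over 20 random draws.

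| Starters | Drop the whole woman | Keep her pre-ART periods | Gain (points) |
|---|---|---|---|
| 0 | 89.1% | 89.1% | 0 |
| 3 | 87.2% | 87.5% | 0.3 |
| 6 | 85.1% | 85.7% | 0.6 |
| 10 | 82.0% | 83.3% | 1.3 |
| 12 | 79.8% | 81.6% | 1.8 |
| 15 | 76.6% | 78.9% | 2.3 |

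Most of the fall down each column comes from ART starts themselves. Only the last column is due to the rule. The gain is small because, in this within-woman calculation, a woman with a single retained period adds nothing to a treatment contrast; only those with two retained periods help.

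**The case against.** **The data are not lost.** This stands. The HIV evaluation section promises separate analysis and description, adverse events are reported for any participant, and the interim mucosal review of the first 25 women to complete the first gel arm is not restricted to the intention-to-treat set. A reader might infer that these women disappear from the safety record; the documents do not support that. What they leave is the main randomised comparison, and for Objective 1 only if this set applies there.

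**The analysed women would be a healthier group, biasing the result.** A reader might infer this from the link the Background draws between low CD4 counts and higher shedding. But each woman is her own control, so removing high shedders does not in itself bias the within-woman contrast. It would do so if the gel effect varied with disease stage, or if starting ART depended on product or response. The documents show neither: district committees control access to the ART programmes, and the two gels are blinded.

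**Up to 17% of women could leave.** 10/60 = 16.7% is a ceiling. It spends the whole enrolment margin on ART starts, whereas the protocol gives that margin for loss to follow-up as well. The protocol cites about 2,500 people treated nationally out of 600,000 (0.4%), though it also says access is widening.

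**The Data analysis section contradicts the definition.** It says "women who use study gel 6 of 9 days or more will be included in the per protocol analysis" and that "those who do not meet this criterion will be included in the intention to treat analysis", which might be read as two non-overlapping sets. That reading fails. Non-adherent women belong in an intention-to-treat set, and the randomisation section admits every randomised woman and excludes only ART starters. Adherent women are therefore in both sets, and per-protocol is a subset. The wording is loose, not wrong.

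**Setting aside post-ART samples is also a post-randomisation exclusion, and such handling belongs in the SAP.** The first half is correct, and the analysis must be labelled accordingly. The second half does not excuse the rule: the protocol itself fixes it, and a SAP that followed it would inherit it.

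**Conclusion.** The point holds as a defect of definition. A set that removes randomised women for a later event is not intention-to-treat, and the reason given supports only part of what is removed.

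Its size is modest. For shedding, the rule costs about 0.3 to 2.3 points of power for 3 to 15 starters, under the assumptions shown, and it does not overturn the sample size. For safety, the cost is the completeness of the randomised comparison. That cannot be quantified without a start rate, and it rests on the assumption that the set as defined applies to Objective 1, which the protocol does not say. This merits correction but does not threaten the validity of the trial.

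**What to change.** Reword the Randomization and dispensing and HIV evaluation sections:

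- Intention-to-treat contains all randomised women, with each period analysed as assigned.
- All randomised women enter the Objective 1 analyses, whether or not they start ART.
- For shedding only, samples taken after ART start are set aside and earlier samples are kept. That analysis is labelled as excluding post-ART samples and is not called intention-to-treat.
- A sensitivity analysis of shedding uses all samples.
- The separate description of women who start ART can stay as a supplement.

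Optionally, one sentence under Data analysis could state that per-protocol is a subset of intention-to-treat.

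The cost is this wording and slightly more analysis work. The medication log, scheduled in Table 3 from enrolment to the closing visit, should supply ART start dates. The remaining drawback is that the main shedding analysis is not strict intention-to-treat. No visit, procedure or clinical rule changes.
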